### Procedure for recruitment

Chinese-speaking international students (undergraduate and postgraduate) will be recruited directly from the community. This will be predominantly through the Glasgow University Counselling and Psychology Service and also using posters, direct emails and adverts; as well as through the University Chinese society.

Individuals who respond to the adverts will be directed to the study recruitment website where they can read the Participant Information Sheet and find out more about the study and how to take part. They can then contact the research team to ask for further information. A consent form will be sent to all potential participants along with an Eligibility Questionnaire and a further copy of the Participant Information Sheet.

The consent form requests permission to use anonymised eligibility data even if a participant is not suitable for the study in order that we can better understand take-up and drop-out and describe basic demographic details of those not taking up the study. The eligibility questionnaire collects demographic information, such as participants’ age, date of birth, current education status, gender, whether they have access to the internet, information regarding previous or ongoing mental health treatment and also whether they have at any point been diagnosed with low mood or anxiety. The eligibility pack also includes the PHQ-9 [13] and GAD-7 [14] in order to assess mood.

### Randomisation

Once eligible participants have completed the consent form, they will then be randomly assigned to one of two groups. Participants’ ID numbers will be passed to a separate researcher who will use the randomisation function in Excel to remotely assign participants to the immediate access (IA) group or the delayed access control (DA) group. As it is a pilot study, we will not stratify for any variables during randomisation. The randomisation will be done remotely by a researcher who will not be involved in the final data analysis. After randomisation, the two groups of participants will be followed up in exactly the same way. The most important advantage of remote, computerised randomisation is that it minimises allocation bias, balancing both known and unknown prognostic factors, in the assignment of treatments.

All participants will then be emailed the necessary information regarding the study for the two different groups of participants. Participants will have the option of contacting the research team to get practical support in accessing the online package. All such contacts will be recorded in a contact log (participant, time/frequency and content of support need).

### Immediate access (IA) group

Participants randomised to IA will be given log in details for the LL online intervention and will begin receiving weekly support via automated emails in either Mandarin or Cantonese. In addition, personalised short weekly support sessions will be offered by email from a Chinese-speaking counsellor. Support will focus on encouraging module completion and practicing what has been learned. Copies of emails will be retained to check adherence to the Plan, Do, Review model [15] of support. This model uses two worksheets (planner and review sheets) to apply what is learned in practice.

### Delayed access control (DA) group

Participants randomly allocated to the delayed access group will be informed that they will be given access to the online course after a delay of 3 months. As in the IA group, all participants will continue with any usual treatment as required.

### Intervention

The “Living Life” Chinese version intervention is an online set of resources including e-books, printable worksheets—together with linked audio modules. The package contains eight modules that teach a range of CBT-based life skills. Modules involve slides with audio and take between 25 and 45 min to complete. Each focuses on a different common problem faced by people when they feel low or anxious.

The eight modules are:Session 1: “Why do I feel so bad?”—An introduction to the CBT model and the “vicious cycle” of low mood. This module helps participants to understand why they feel the way they do and how their thoughts, feelings, physical symptoms and behaviour are linked.Session 2: “I can’t be bothered doing anything”—This module aims to tackle reduced activity. Users are encouraged to consider the things that they have stopped doing or are prevented from doing as a result of their low mood or anxiety and make a plan to re-establish these activities in order to improve their mood.Session 3: “Why does everything always go wrong?” – Skills to help tackle negative thinking are taught in this session. Participants are taught how to label unhelpful thoughts, identify their negative thinking patterns and are given various tools to turn these thoughts around to create more positive ones.Session 4: “I’m not good enough”—This session teaches how confidence is developed and the ways in which low self-esteem can impact on mood. Confidence building techniques are taught in this module.Session 5: “How to fix almost everything”—A problem-solving module teaching the “Easy 4 Step Plan (E4SP)” which shows participants how to break down problems and tackle small parts of the problem in order to overcome challenges. The session focuses on resolving practical problems that users may be experiencing.Session 6: “The things you do that mess you up”—This session addresses unhelpful behaviours that may be worsening mood. Participants are encouraged to recognise problem behaviours and create a plan for reducing them.Session 7: “Are you strong enough to keep your temper?”—Participants learn to recognise the things that cause them to feel irritable or angry (their “buttons”) and the physical symptoms they experience when they feel angry. They are then taught techniques for managing their anger and reacting differently to challenging people and situations.Session 8: “10 things you can do to feel happier straight away”—The final module teaches key lifestyle choices that can improve mood including healthy eating, exercise and closeness with others.

Users are encouraged to make an individualised plan at the end of each session using a Plan, Do, Review structure [15] in order to apply the techniques learned in the modules. The intervention is designed to be accessible and easily understood. This is achieved by omitting complicated CBT terms and replacing these with simpler language, as seen in the titles of the modules. The language used in the modules includes everyday terms to describe symptoms such as stress, distress and low mood rather than more formal diagnostic terms depressive disorder, depression and anxiety etc. This simple way of communicating CBT used is highly accessible [16] and effective [17, 18].

### Cultural adaptations

Simple/traditional Chinese, Mandarin and Cantonese versions of the materials have been made available. A series of facilitated focus groups identified changes required to culturally adapt content for use with this target population. The main finding from the focus groups was that participants felt that all of the research materials (including advertisements and questionnaires) and the online intervention should be written in the Chinese language. The modules were already in Chinese but all of the menu items and any written information on the home page had to be translated. Additionally, English language versions of the modules were removed from the website.

Opinions relating to preferred support were also collected during the focus groups. The majority of participants in the focus groups stated that support sessions delivered via email would be acceptable and in most cases preferable to telephone support. Therefore, the support sessions will be delivered by a support worker based at the student counselling service via weekly emails to participants. These emails will be written in Chinese, as this was expressed as important by participants.

Finally, the layout of the website was adapted following comments from the focus group participants. The full results of the focus group study will be published separately.

### Support

Participants will have the option to sign up to receive weekly automated support emails with the option of traditional or simple Chinese script. As recommended by the focus group work, participants will receive a regular personalised support element; delivered by a Chinese-speaking trained counsellor via email. This will test the support offered for use in the later substantive RCT.

The support is protocol driven and focused on encouraging use and application of the intervention. It is designed to encourage an individualised plan to be made at the end of each session using a Plan, Do, Review structure, with a focus on making changes in their lives and using the materials to support them in doing this. Therefore, the online intervention uses a structured, guided self-help approach that may be appealing to students.

### Follow-up data collection

The main follow-up point will be at 3 months with an additional follow-up assessment at 6 months (see Table 1). The primary outcome in the future substantive study will be PHQ-9 at 3 months.

**Table 1 Tab1:** Timing of measures taken during the study

Baseline	3 months	6 months
Demographic data	PHQ-9	PHQ-9
PHQ-9	GAD-7	GAD-7
GAD-7	WSAS	WSAS
WSAS	CSQ-8 (IA group only)	CSQ-8 (DAC group only)

Baseline measures include age, gender, course type (undergraduate/post-graduate), ethnicity, mood, anxiety, social function, (Chinese versions where available), antidepressant medication and current psychiatric treatment.

The following measures will be completed online:

#### Patient health questionnaire-9 [13]

PHQ-9 is an open access mood rating questionnaire consisting of nine questions mirroring DSM-IV depression diagnostic criteria and each rated 0–3 giving a maximum score of 27. The use of PHQ-9 on Chinese general hospital outpatients showed a Cronbach’s alpha coefficient of 0.857, suggesting the good internal consistency [19]. Cut-off scores are used to label depression severity as 0–4: minimal depression; 5–9: mild depression; 10–14: moderate depression; 15–19: moderately severe depression; and 20–27: severe depression.

#### Generalised anxiety disorder 7 [14]

The GAD-7 is a seven item questionnaire focusing on symptoms of anxiety. Each item is rated according to the frequency of the described problem in the past 2 weeks. The responses are scored as follows: 0 = “not at all”, 1 = “several days”, 2 = “more than half the days”, 3 = nearly every day’ with a maximum score of 21. The use of the GAD-7 on Chinese general hospital outpatients found a Cronbach’s alpha coefficient of 0.898 and the test-retest reliability was 0.856, indicating good reliability and validity [20]. Scores of 0–5 on this measure indicate mild anxiety, 6–10 = moderate anxiety, 11–15 = moderately severe anxiety and 15–21 = severe anxiety.

#### Work and social adjustment scale [21]

The Work and Social Adjustment Scale (WSAS) assesses social functioning. The WSAS is a five-point questionnaire and addresses issues relating to the individual’s everyday life and functioning and how their mood disorder is affecting these areas. Responses are given on a scale of 0–8, with higher scores indicating higher level of impairment. Those scoring over 20 are likely to have significant problems in their social functioning. The Cronbach’s alpha coefficient of the Chinese version of WSAS with Chinese college students was 0.849 [22].

#### The client satisfaction questionnaire (CSQ-8) [23]

The English language version of the CSQ-8 will be administered post intervention as a measure of satisfaction. The CSQ-8 is an eight-item questionnaire, rated using a four-point Likert scale. Scores range from 8–32, with higher scores indicating greater satisfaction with the intervention in question. The internal consistency of the CSQ-8, measured by Cronbach’s alpha coefficient, ranged from 0.83 to 0.93 in English-speaking populations [23].

In addition, a check of contamination (use of the website by the DAC), use of other online/book resources and any adverse consequences of using the site in the IA arm will be assessed at 3 months.

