### Research questions

Primary question:Is the study design feasible—is it possible to recruit Chinese-speaking international students from a University setting, randomise participants and collect data at baseline, 3 months and 6 months?

Secondary questionsb.To what extent will participants adhere to the online intervention?c.Is the Living Life package acceptable to Chinese-speaking students?d.How many participants will be needed for a sufficiently powered future RCT?

By gathering information about uptake, retention, ability to gather data, as well as obtaining an estimate of treatment effect, it will be possible to complete a power calculation to estimate the sample size required for the future substantive study.

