### Participants

The aim is to recruit up to 50 participants in total to provide an indication of the take-up, use and impact of the course on low mood or anxiety; and identify any problems with recruitment, delivery of the intervention and completion of evaluation measures. Such problems could be recruitment difficulties, drop-out during the intervention, poor adherence to the online course and failure to complete follow-up measures.

Inclusion criteria:

To enter the study, individuals must be Chinese-speaking (Mandarin or Cantonese) international students aged 18 years of age or more, registered as students (undergraduate or postgraduate) at the University of Glasgow and living in the UK for the next 2 months. This is to ensure they are in the UK when using the intervention so that appropriate support can be offered in the event of identified risk. Current symptoms of depression with the score 5+ on the PHQ-9 [13] depression questionnaire and/or a score of 5+ on the generalised anxiety disorder −7 (GAD-7) [14] scale (Chinese language versions) must be present for eligibility. Participants will be required to have broadband web access and also be willing and able to use the online course.

Exclusion criteria:

Participants will be excluded if they do not fulfil the inclusion criteria or are currently receiving specialist mental health treatment or current psychotherapy/counselling. Students who are on antidepressants will not be excluded, but we will record the drug, dose and length of time on the medication.

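### The CSQ-8 is to be given in English, without a stated reason, although the protocol's main focus-group finding was that questionnaires should be in Chinese

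*Protocol article*

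**What the plan says.** All references are to the protocol article.

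- **Client satisfaction questionnaire section:** "The English language version of the CSQ-8 will be administered post intervention as a measure of satisfaction". Its internal consistency is said to have "ranged from 0.83 to 0.93 in English-speaking populations".
- **Cultural adaptations:** the main focus-group result is that "participants felt that all of the research materials (including advertisements and questionnaires) and the online intervention should be written in the Chinese language". The same section says that menu items and home-page text were translated, that "English language versions of the modules were removed from the website", and that support emails will be in Chinese because participants considered this important.
- **Research questions:** secondary question (c) asks "Is the Living Life package acceptable to Chinese-speaking students".
- **Participants:** the PHQ-9 and GAD-7 used for eligibility are the Chinese forms ("scale (Chinese language versions) must be present for eligibility"). The language criterion is that "individuals must be Chinese-speaking (Mandarin or Cantonese) international students aged 18 years of age or more, registered as students". No criterion on reading English is stated.
- **Follow-up data collection:** the list of baseline measures carries the qualifier "social function, (Chinese versions where available". Table 1 places the CSQ-8 at 3 months for the immediate access arm and at 6 months for the delayed arm, with none at baseline.

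**The concern.** The trial ran focus groups to find out how its materials should be adapted, and their main message named questionnaires explicitly. The website and the support emails were changed accordingly. One instrument then departs from that message, and it is the one that asks participants directly what they thought of the package.

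If some respondents misread items, or skip them because they are in English, the resulting score cannot be separated from their real view of the package. The benefits section expects the satisfaction data to show how such websites are best delivered and supported, so the score will be used. A pilot is also where instruments for the later trial are tried out. An English form used here without a check would go forward with its performance in this population unknown.

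**Working it through.** No sample-size, power or error-rate calculation applies. The check is a comparison of sections, with two small pieces of arithmetic.

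**1. Is the scale described consistently?** Eight items scored 1 to 4 give a minimum of 8 × 1 = 8 and a maximum of 8 × 4 = 32. This matches the stated range of 8 to 32, so the scoring is not in question.

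**2. How does the CSQ-8 compare with the other three questionnaires?**

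| Instrument | Language evidence in the article | Reliability cited (Cronbach's alpha) | Population of that figure |
|---|---|---|---|
| PHQ-9 | Chinese form at eligibility | 0.857 | Chinese hospital outpatients |
| GAD-7 | Chinese form at eligibility | 0.898 | Chinese hospital outpatients |
| WSAS | Covered by the baseline qualifier on Chinese versions | 0.849 (Chinese version) | Chinese college students |
| CSQ-8 | English form specified | 0.83 to 0.93 | English-speaking populations |

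The CSQ-8 is the one exception among four, both in language and in the population behind its reliability figure.

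**3. Does the qualifier about available Chinese versions cover it?** No. The qualifier sits in the sentence on baseline measures, and Table 1 shows that the CSQ-8 is not taken at baseline. Nothing in the article says that a Chinese CSQ-8 is unavailable, explains the English form, or plans a translation or a comprehension check.

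**4. Is this only missing detail?** No. An article may leave much to the full protocol, but here it affirmatively specifies the English version.

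**5. How many responses are affected?** The aim is up to 50 participants, half per arm: 50 × 0.5 = 25. So there are at most about 25 CSQ-8 forms in the immediate access arm at 3 months and about 25 in the delayed arm at 6 months, before drop-out. All of them would be in English.

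**6. Can the bias be sized?** No. The article gives no data on English proficiency, on comprehension of the items, or on the performance of the English form in Chinese speakers. Neither the amount nor the direction can be derived.

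**The case against.** The strongest defence is that this is a disclosed choice about a secondary instrument. The article says openly that the form is English and labels its alpha as coming from English-speaking populations, so nothing is misrepresented. Every participant is a registered undergraduate or postgraduate at a UK university, so some working English is likely, and the scale is short. The pilot is unfunded and largely descriptive, and the CSQ-8 has no stated part in the future sample-size calculation, which rests on the PHQ-9 and retention. All of this stands, and it limits the weight of the point. It does not supply the missing reason for the exception.

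Several stronger readings are tempting, and the document does not support them:

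- *That the focus groups required Chinese questionnaires.* Participants expressed a view about what should be done. The protocol reports it as the main finding and acted on it elsewhere, but it was not a binding condition.
- *That the acceptability result depends on English reading ability.* This is an inference. It could depend on it in part; no evidence in the document shows that it does.
- *That question (c) has no other evidence.* Take-up, course completion and drop-out also inform acceptability. The CSQ-8 is the only named direct satisfaction measure, which is a narrower statement.
- *That an English form would lower questionnaire completion, part of the primary feasibility outcome.* No order of administration is given, since a position in Table 1 is not an order of completion. Nothing shows an effect on the other questionnaires.
- *That an existing translation team makes the change almost free.* The article says that site text had to be translated but not by whom.

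It can also be argued that a study-made translation gives up a published form for an unvalidated one. That has force against outright replacement, and much less against showing both texts together.

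**Conclusion.** The inconsistency is real. The article specifies an English CSQ-8, supported only by reliability in English-speaking populations, against its own main focus-group finding and without a reason. Responses could therefore partly reflect comprehension of English.

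The point is worth correcting but limited in reach. It affects one of four questionnaires and one secondary research question. It does not touch the PHQ-9, the feasibility rates as defined, or the planned power calculation.

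The conclusion assumes that the full protocol does not contain a justification that the article left out. It does not assume poor English among participants, only that the article neither requires nor checks English reading.

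**What to change.** In the client satisfaction questionnaire section:

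1. Administer the CSQ-8 with a forward- and back-translated Chinese text, in simplified and traditional script, shown beside the published English items.
2. Report Cronbach's alpha in this sample descriptively. With at most about 25 respondents per time point it will be imprecise and should not be presented as validation.
3. Keep the cited alpha, but state that it applies to the English form in English-speaking populations and does not establish reliability here.

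Keeping the English items in view preserves the published wording and brings the section into line with the one on cultural adaptations.

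The cost is modest: translating and back-translating eight items. The Chinese text would not be separately validated, so scores should not be benchmarked against English norms.

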## Methods/design

### Overview

This is a pilot study with a randomised controlled design. This study will investigate the possibility of delivering the culturally adapted Living Life online life skills resource to Chinese-speaking international students. In this RCT, 50 % of participants will be randomly allocated to receive immediate access (IA) to the Living Life (LL) online intervention and 50 % will be in the delayed access control group (DA). The primary end point is 3 months at which point the control arm will be invited to begin the intervention. A further follow-up point will be at 6 months post-randomisation. This 6-month time point was chosen as a comparative, reasonable follow-up length to fit the structure of the academic year.

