### Benefits to participants

Participation within this research will allow Chinese-speaking international students who are experiencing symptoms of anxiety and depression to take part in an online CBT-based course for stress and low mood in their own language. There is evidence supporting the use of the CBT self-help approaches for depression and anxiety by teaching problem-solving skills, assertiveness, tackling negative thinking and increasing activity levels [11, 12, 24, 25]. By using the package, it is hoped that participants may learn new skills to help with symptoms of low mood, anxiety or depression. The satisfaction data will help us to gain a key insight into how online websites can be best delivered and supported in this setting.

Little previous research has examined the presence of adverse impacts of using cCBT. We are therefore monitoring progress using support contacts and in addition have added a question at follow-up to examine adverse consequences in the IA arm. It is unlikely that participants’ condition will worsen significantly during the study. We do however have risk management protocols in place if needed, as outlined in the following section.

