#### Risk management

The Participant Information Sheet will give suggestions for sources of additional/urgent support including their GP, NHS24, student counselling, A + E and Samaritans. Additionally, the study website contains a tab detailing sources of urgent help. Finally, all participants will be assigned a Chinese-speaking support worker based at the University Student Counselling who will contact them each week to monitor their progress. Therefore, participants will have the opportunity to discuss any deterioration in their mood, in which case the support worker would inform the clinical lead of the study, CW.

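### The adverse-consequences question is limited to the immediate access arm, so delayed access participants are not systematically asked about harm after using the same course

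*Protocol article*

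**What the plan says.** Two sections of the protocol article describe the structured harm question.

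- The client satisfaction questionnaire (CSQ-8), closing paragraph: "any adverse consequences of using the site in the IA arm will be assessed at 3 months". This gives both the arm and the time.
- Benefits to participants: the authors "have added a question at follow-up to examine adverse consequences in the IA arm". This gives the arm again, but no month. The reason offered is "Little previous research has examined the presence of adverse impacts of using cCBT".

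The rest of the design bears on this as follows.

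- Overview: "The primary end point is 3 months at which point the control arm will be invited to begin the intervention". It adds: "A further follow-up point will be at 6 months post-randomisation". Use of the course by the DA arm therefore falls mainly between the two follow-up points.
- Follow-up data collection, Table 1: PHQ-9, GAD-7 and WSAS are collected in both arms at baseline, 3 and 6 months. The CSQ-8 goes to IA at 3 months, and the 6-month column has "CSQ-8 (DAC group only").
- Randomisation: after allocation "the two groups of participants will be followed up in exactly the same way".
- Risk management: "all participants will be assigned a Chinese-speaking support worker based at the University Student Counselling who will contact them each week to monitor their progress".

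**The concern.** The satisfaction measure follows exposure: each arm completes the CSQ-8 at the follow-up after its first period of access. The harm question does not. It is tied to the IA arm in both places where it appears, and no reason is given for leaving out DA participants once they have had the course.

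This is a stated restriction, not a detail left to a fuller document. It also fits poorly with the statement in Randomisation that both groups are followed identically.

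What is at stake is how much the pilot can say about harm. The protocol presents the question as a response to thin evidence, then puts it to about half of the people who will be offered the intervention. The CSQ-8 section also plans to check at 3 months whether DA participants used the website early. As written, anyone found to have done so would have been exposed and still not be asked about adverse consequences.

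**Working it through.** The protocol states no adverse-event rate or precision target, so there is no figure of its own to reproduce. The arithmetic below is for scale only.

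**Inputs from the protocol article**
- Up to 50 participants in total (Participants).
- Equal allocation (Overview), so 50 × 0.5 = 25 per arm.
- Asked about harm as written: IA only, 25 people.
- Asked if DA participants were included after their own exposure: up to 25 + 25 = 50.

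**Assumptions not in the document**
- Recruitment reaches 50 and every DA participant takes up the course.
- Follow-up is complete, or alternatively 20% are lost in each arm (25 × 0.8 = 20; 50 × 0.8 = 40).
- True reporting rates of 2%, 5% and 10% are illustrative.

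**Upper limit after zero reports.** The exact one-sided 95% limit is 1 − 0.05^(1/n).

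| Follow-up | IA only | IA and DA |
|---|---|---|
| Complete | n = 25: 1 − 0.05^(1/25) = 11.3% | n = 50: 1 − 0.05^(1/50) = 5.8% |
| 20% lost | n = 20: 1 − 0.05^(1/20) = 13.9% | n = 40: 1 − 0.05^(1/40) = 7.2% |

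If only 12 of the 25 DA participants used the course, with no loss, n = 25 + 12 = 37 and the limit is 1 − 0.05^(1/37) = 7.8%. Partial take-up therefore shrinks the gain but does not remove it.

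**Chance of at least one report.** This is 1 − (1 − p)^n, with complete follow-up.

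| True rate p | n = 25 | n = 50 |
|---|---|---|
| 2% | 40% | 64% |
| 5% | 72% | 92% |
| 10% | 93% | 99.5% |

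**What a control-arm event question would give.** Suppose a neutrally worded event question were put to both arms at 3 months. The approximate 95% half-width for the difference in proportions is 1.96 × √(2p(1 − p)/25).
- p = 5% in both arms: about 12 percentage points.
- p = 20% in both arms: about 22 percentage points.

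Such a comparison would be too imprecise to carry much weight in a study of this size.

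**The case against.** The strongest reply has five parts.

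1. **Symptom worsening is already measured in both arms.** Table 1 collects PHQ-9, GAD-7 and WSAS from everyone at 3 and 6 months. A reader might infer that deterioration while waiting goes unrecorded, or that harm has no control comparison at all. The document does not support that: the scales give a randomised comparison at 3 months. What the article does not state is a summary of worsening. This part of the reply stands.

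2. **The item cannot apply to unexposed controls.** It asks about consequences of using the site, and at 3 months DA participants have not yet been offered it. Leaving them out at that point follows from the wording and is not a fault. This stands, except for DA participants who used the site early. It does not explain their absence at 6 months.

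3. **Other routes exist.** Weekly support-worker contact is worded for all participants, and Benefits to participants names support contacts as a form of monitoring. A reader might infer that DA users supply no harm information whatever; that goes too far. But these contacts give people a chance to raise a problem. They are not a fixed question put to everyone, and the protocol itself treats the question as additional to them.

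4. **The article is condensed.** Table 1 does not list the harm item even at 3 months, so its absence from the 6-month column proves little on its own. Benefits to participants names no month, so a 6-month repeat in the IA arm is not excluded. Both points are fair, but the finding rests on the explicit IA restriction in two sections, which shuts out DA participants at either time.

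5. **The later trial does not depend on this.** A reader might infer that a one-sided harm rate will be carried into the main trial. The protocol says only that PHQ-9 and retention data feed its sample size, so that inference is unsupported.

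**Conclusion.** The point holds in a limited form. The structured adverse-consequences question is confined to the IA arm, with 3 months the only time stated. DA participants are offered the same course from month 3 and are followed up at 6 months without a stated harm question. Up to 25 of 50 people eventually offered the course are therefore not systematically asked about harm after exposure.

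In size, this is the difference between ruling out harm rates above 11.3% and above 5.8% if nobody reports anything, or 13.9% and 7.2% with an assumed 20% loss. These are best-case contrasts: they depend on recruiting the maximum and on full DA take-up, which the pilot exists to find out.

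The feasibility aims are not threatened. The change is still worth making, because the protocol singles out harm as an evidence gap and the missing half can be collected at almost no cost.

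**What to change.** 1. Amend the closing paragraph of the CSQ-8 section, Benefits to participants and Table 1 so that the same adverse-consequences question is put to DA participants at 6 months, mirroring the CSQ-8. List the item in Table 1 for each arm and time at which it is asked.
2. Put the question at 3 months to any DA participant whom the contamination check shows to have used the site early.
3. Report by arm at 3 months the change from baseline and the number worsening on both PHQ-9 and GAD-7, as the randomised comparison for deterioration. Both scales are needed because Participants allows entry on anxiety score alone. Define worsening in advance on the scores, not only as a move between PHQ-9 severity bands: a change from 9 to 10 crosses a band, while a change from 5 to 9 does not.
4. Report answers to the harm question with the number of people who used the course and were asked as the denominator. Do not assume that IA access ends at 3 months, since the article does not say so.

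The cost is one extra item on an online form already being sent, and one extra table from data already collected. A neutrally worded event question to both arms at 3 months is optional; it would add a comparison, but an imprecise one.
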